### Patient recruitment and baseline data collection

The day before surgery (or Friday for those who will undergo surgery next Monday), investigators who are authorized by the principal investigator will visit patients who are scheduled for upper abdominal or noncardiac thoracic surgery to identify potential participants according to the inclusion and exclusion criteria. They will then invite the potential participants for study participation.

For patients who meet the inclusion/exclusion criteria and provide written informed consent, baseline data including demographic data, preoperative diagnosis, medical history, preoperative medication, surgical history, as well as main results of physical, laboratory, and instrumental examinations will be collected.

### Randomized, blinding and study drug administration

Random numbers were generated in a 1:1 ratio using the SAS 9.2 software package (SAS Institute, Cary, NC, USA) by a biostatistician. Randomization will be stratified according to the type of surgery (upper abdominal or noncardiac thoracic surgery). Study drugs (penehyclidine hydrochloride 1 mg/1 ml, or water for injection 1 ml) are provided as clear aqueous solution in the same 1 ml ampoules (manufactured by Chengdu List Pharmaceutical Co., Ltd., Sichuan, China) and labeled according to the randomization results by a biostatistician and a pharmacist who are independent of patient recruitment and data collection. The results of randomization are sealed in the envelopes and stored at the site of investigation until the end of the study.

During the study period, consecutively recruited patients will be assigned sequential numbers according to which the study drugs will be dispensed by a study coordinator. Study drugs are administered by inhalation in the night (7 pm) before surgery, in the morning (7 am) of surgery, and then every 12 hours until postoperative day 2, resulting in a total number of 7 inhalations. Study drug inhalation is performed with a jet nebulizer (DNA100, manufactured by Congren Medical Equipment Co., Ltd., Xiamen, China) for extubated patients or a vibrating mash nebulizer (Agrogen Professional Nebulizer System, AG-AP6000CH, Aerogen Ltd, Ireland) for patients with mechanical ventilation. Before inhalation, study drugs (penehyclidine hydrochloride 0.5 mg/0.5 ml for patients in the penehyclidine group, or water for injection 0.5 ml for patients in the placebo group) are diluted with normal saline to 6 ml. The performance of each study drug inhalation is recorded in the CRFs.

Patients, investigators, and healthcare team members are all blinded to the study group assignment throughout the study period. In case of an emergency (such as development of a severe adverse event), attending physicians or surgeons can request unmasking of the treatment allocation. These situations will be documented; but analyses will be performed on the intention-to-treat population.

### Anesthesia and perioperative management

Intraoperative monitoring include electrocardiogram, pulse oxygen saturation, noninvasive blood pressure, airway pressure, end-tidal carbon dioxide concentration, nasopharyngeal temperature, urine output, and bispectral index (BIS) value. Intra-arterial pressure (and derivative parameters such as stroke volume variation by FloTrac system) and central venous pressure are monitored when considered necessary.

Anesthetic premedication is not administered. Prophylactic antibiotics (the first or second generation cephalosporin, with or without metronidazole, or cephamycins) are administered 30 minutes to 1 hour before surgical incision. The duration of prophylactic antibiotic treatment is less than 48 hours. The choice of antibiotics and the duration of prophylactic antibiotic therapy are decided according to the *Guiding Principles of Clinical Use of Antibiotics* (published by Chinese National Health and Family Planning Commission in 2015) http://www.nhfpc.gov.cn/zwgkzt/wsbysj/200804/18544.shtml. Therapeutic antibiotic agents are only indicated in patients who are diagnosed with infection.

General anesthesia with endotracheal intubation is performed for all patients. Anesthesia is induced with intravenous propofol or etomidate, sufentanil, and rocuronium, or cisatracurium, and maintained with intravenous propofol, remifentanil and/or sufentanil, and rocuronium or cisatracurium, with or without inhalational sevoflurane and/or nitrous oxide. Neuraxial block is performed depending on the decision of attending anesthesiologists. BIS value is maintained between 40 and 60. Mechanical ventilation is established with a tidal volume from 6 to 8 ml/kg, a positive end-expiratory pressure from 0 to 5 cm H2O, a frequency from 12 to 16 breaths per minute, and 50% oxygen (mixed with nitrous oxide or air). Higher oxygen concentration is administered during one-lung ventilation. Fluid management is performed according to routine practice. Packed red blood cells are transfused to maintain a hemoglobin level above 7 g/dl. Anticholinergics are prohibited unless being used for the treatment of bradycardia, in which case atropine is administered.

At the end of surgery, patients are transferred to the postoperative care unit (PACU) after extubation and monitored for at least 30 minutes before being sent back to the general wards. For patients who are transferred to the intensive care unit (ICU) with endotracheal intubation, propofol and/or dexmedetomidine sedation are provided in addition to opioid analgesia; mechanical ventilation is performed with bilevel ventilation mode (established with a low level at 3 to 5 cm H_2_O, a high level between 13 and 16 cm H_2_O, and a trigger flow at 2 to 3 l/min; PB 840 ventilator, Puritan-Bennett Corp., Mervue, Ireland). Patients are extubated as soon as they meet the criteria of extubation (regain consciousness and airway protective reflex, normal circulatory status and temperature, no residual neuromuscular blockade). For patients requiring mechanical ventilation of more than 24 hours, a ventilator weaning protocol is executed in order to extubate patients as soon as possible (Additional file 2). For patients with acute respiratory failure, noninvasive positive pressure ventilation is used to promote early extubation or to avoid reintubation. For all patients after extubation, low-flow supplemental oxygen is routinely provided during the day of surgery.

During the postoperative period, patient-controlled analgesia (either intravenous or epidural) is provided for up to 3 days after surgery. The target is to maintain a Numeric Pain Rating Scale (NPRS, an 11-point scale where 0 = no pain and 10 = the worst pain) pain score of 3 or less. Nonsteroidal anti-inflammatory drugs are administered when considered necessary and without contraindications. Other treatments including chest physiotherapy, early mobilization, removal of nasogastric tube, parenteral or enteral nutrition, and intravenous respiratory medications (such as expectorants, theoclears and glucocorticoids) are administered according to routine practice.

During the study period, inhalations of any respiratory medications for prophylactic purpose other than the study drugs are prohibited. However, for patients who develop PPCs, inhalation of respiratory medications is allowed. For those who develop harmful effects or clinical deterioration, the dose of study drugs can be decreased or the study drug administration can be discontinued on request of participants, attending surgeons or investigators. These situations will be recorded in the CRFs.

### Patient follow-up and outcome assessment

Patients will be followed up twice daily until postoperative day 2, once daily from postoperative days 3 to 6, and then weekly until 30 days after surgery. Intraoperative data including type and duration of anesthesia, uses and doses of anesthetics, analgesics and other drugs, parameters of mechanical ventilation, fluid balance and transfusion of blood products, as well as type and duration of surgery will be collected. The final cumulative ARISCAT risk score will be calculated just after the surgery. Postoperative data including NRS pain scores, analgesic consumption, respiratory management, return of gastrointestinal function, start of nutrition, occurrence of complications and related treatment, admission to the ICU, duration of hospital stay, and any events that lead to return or readmission to hospital after hospital discharge will be recorded. Any adverse events or complications that occur during the study period will be promptly treated according to routine practice. For patients who deviate from the intervention protocol, deviations will be corrected when possible and follow-up will be completed. For patients who withdraw consent, the last follow-up results will be regarded as the final results.

#### Primary outcome

The primary outcome is the incidence of PPCs within 30 days after surgery. In the present study, PPCs are generally defined as any condition that affects the respiratory tract system and may adversely influence patients’ outcome [1]. The diagnostic criteria of each individual PPC are listed in Table 2 [3]. We adopt the Clavien-Dindo Classification to categorize PPCs into five major groups [12, 13], and PPCs of grade II or above will be used to calculate the incidence of PPCs (Additional file 3). If a PPC occurs during the follow-up period, the date of earliest diagnosis and the evidences according to which the diagnosis is made will be documented.

**Table 2 Tab2:** Definitions of PPCs

Complications	Definition
Respiratory infections	Receiving antibiotics for a suspected respiratory infection and met at least one of the following criteria: new or changed sputum, new or changed lung opacities, fever, leukocyte count >12 × 10^9^/L
Respiratory failure	PaO_2_ < 60 mmHg on room air, a ratio of PaO_2_ to inspired oxygen fraction < 300, or arterial oxyhemoglobin saturation measured with pulse oximetry < 90% and requiring oxygen therapy
Pleural effusion	Chest X-ray demonstrating blunting of the costophrenic angle, loss of the sharp silhouette of the ipsilateral hemidiaphragm in upright position, evidence of displacement of adjacent anatomical structures, or (in supine position) a hazy opacity in one hemithorax with preserved vascular shadows
Atelectasis	Lung opacification with a shift of the mediastinum, hilum, or hemidiaphragm toward the affected area, and compensatory overinflation in the adjacent nonatelectatic lung
Pneumothorax	Air in the pleural space with no vascular bed surrounding the visceral pleura
Bronchospasm	Newly detected expiratory wheezing treated with bronchodilators
Aspiration pneumonitis	Acute lung injury after inhalation of regurgitated intragastric contents

*PPCs* postoperative pulmonary complications

#### Secondary outcomes

Secondary outcomes include the time to onset of PPCs (from end of surgery to first diagnosis of PPCs), the number of PPCs (indicate the number of diagnosed individual PPCs), the incidence of postoperative extrapulmonary complications, the length of stay (LOS) in hospital after surgery, and the 30-day all-cause mortality. Postoperative extrapulmonary complications are defined as complications other than PPCs that occur within 30 days after surgery and require therapeutic intervention. For each diagnosed extrapulmonary complications, the date of earliest diagnosis and the evidences according to which the diagnosis is made will also be documented.

#### Adverse events

An adverse event indicates any unpredictable, unfavorable medical event that occurs during the period of study drug administration. It can be related to the study intervention or otherwise. Exceptional adverse events occurred during anesthesia include (but not limited to) desaturation (PaO_2_ < 60 mmHg or SpO_2_ < 90%), high airway pressure (peak airway pressure > 40 mmHg), hypercapnia (PaCO_2_ > 50 mmHg), difficult airway (failed intubation attempt > 3 times), hypotension (systolic blood pressure < 90 mmHg or a decrease of more than 30% from baseline), hypertension (systolic blood pressure > 180 mmHg or an increase of more than 30% from baseline), bradycardia (heart rate < 40 beats per minute), tachycardia (heart rate > 100 beats per minute). Other possible adverse events occurred during perioperative period include (but not limited to) nausea, dry month, flushing, dizziness, palpitation, somnolence, cough, delirium, etc. These events are diagnosed according to patient’s complains and symptoms (sought by non-directive questioning), physical and mental signs, as well as results of laboratory tests and instrumental examinations. Delirium is assessed with the confusion assessment method for the intensive care unit (CAM-ICU). Any developed adverse events are managed according to routine practice and followed up until they are properly resolved, stabilized or recovered to normal. The information including the diagnosis, date(s) of onset and resolution (if applicable), severity of influence, relationship with intervention, treatment and outcomes (sequelae) are recorded. The occurrence of adverse events will be reported to the ethics committee in the final report.

A severe adverse event indicates any unpredictable medical events that lead to death, threat of life, prolonged length of hospital stay, persistent disability or dysfunction, or other severe event. All severe adverse events will be monitored, managed, followed up and recorded as above, and will be reported to the ethics committee within 24 hours after their occurrence. Harmful consequence resulted directly from study participation will be compensated according to the corresponding legal provisions.

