Theoretically, selective M1 and M3 receptors blockers may have advantages over nonselective blockers (such as tiotropium bromide) for the purpose of bronchodilation [8]. Penehyclidine is a long-acting anticholinergic agent which selectively blocks M1 and M3 receptors [9, 10]. In a pilot randomized controlled trial of our group, 90 elderly (≥65 years) patients who were admitted to the ICU after long-duration (≥3 hours) surgery randomly received inhalation of penehyclidine, ipratropium bromide, or normal saline for 3 consecutive days. The results showed that prophylactic anticholinergic inhalation significantly reduced the incidence of postoperative bronchospasm (1/30 [3.3%] with penehyclidine hydrochloride, 1/31 [3.2%] with ipratropium bromide, and 6/29 [20.7%] with normal saline, respectively, *P* = 0.025) [11]. We hypothesize that, in high-risk patients, prophylactic inhalation of penehyclidine may decrease the incidence of PPCs.

The purpose of this study is to investigate the impact of prophylactic penehyclidine inhalation on the incidence of PPCs in high-risk patients after major surgery.

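### Adverse event onset is limited to the dosing period, so mild untreated events starting after the last inhalation of a long-acting drug are counted nowhere, and the definition conflicts with its own list

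*Protocol article*

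**What the plan says.** The Adverse events section gives the definition: "An adverse event indicates any unpredictable, unfavorable medical event that occurs during the period of study drug administration". It adds "It can be related to the study intervention or otherwise", so relatedness is not a condition. The same section then gives two open-ended lists. One covers the anesthesia period and includes "tachycardia (heart rate > 100 beats per minute". The other opens with "Other possible adverse events occurred during perioperative period" and goes on: "include (but not limited to) nausea, dry month, flushing, dizziness, palpitation, somnolence, cough, delirium, etc". Severe events have their own sentence, which begins "A severe adverse event indicates any unpredictable medical events that lead to death". It repeats the unpredictability condition but sets no dosing limit.

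The section on randomization, blinding and drug administration sets seven inhalations at 12-hour intervals, from 7 pm on the evening before surgery to postoperative day 2. The section on anesthesia and perioperative management allows study drug to be stopped for harm or deterioration. The Background says: "Penehyclidine is a long-acting anticholinergic agent which selectively blocks M1 and M3 receptors". After twice-daily visits to day 2, the follow-up section schedules visits "once daily from postoperative days 3 to 6, and then weekly until 30 days after surgery", and it refers to adverse events over the study period as a whole. Under Secondary outcomes, extrapulmonary complications are counted to day 30 if they need treatment, and 30-day all-cause mortality is compared.

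**The concern.** The onset rule closes when dosing closes. For a drug that the article presents as long-acting, and whose lasting effect the Discussion cites as an advantage, effects of the last doses may first appear after the rule has stopped counting. Patients are still being seen then, so the information is within reach but has no place in the adverse event table.

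Two further problems sit in the same text. The unpredictability condition, read as written, would exclude known effects of an anticholinergic, yet the section names several of them as adverse events. And if the dosing period means each patient's own dosing, the window shortens for patients taken off study drug because of harm. Should such stopping differ between arms, observation time for adverse events would differ too.

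The safety data matter. The Discussion promises evidence on safety as well as effectiveness. The Data analysis section gives the pilot's confirmation of safety as the reason for planning no interim analysis, but that pilot had 30 penehyclidine patients. Even zero events of a given kind among 30 leaves a one-sided 95% upper bound of 1 − 0.05^(1/30) = 9.5%. This trial, with 432 planned per arm, is a much larger source of safety data.

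**Working it through.** **1. Length of the literal window.** The inputs are the first dose at 7 pm on day −1, the 12-hour interval, and the last dosing day, postoperative day 2.
- Doses: 1 (7 pm, day −1) + 2 × 3 (7 am and 7 pm on days 0, 1 and 2) = 7. This reproduces the stated number.
- First to last dose: (7 − 1) × 12 h = 72 h, ending at 7 pm on postoperative day 2.
- Postoperative follow-up outside the window: 30 − 2 = 28 days, and 28/30 = 93%.
- Daily visits after the window closes: days 3, 4, 5 and 6, so four, followed by the weekly contacts.

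The 93% is a share of calendar time, not of events. All seven exposures and the whole anesthesia period lie inside the window, so drug-related events should be concentrated there.

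**2. Where an event starting on, say, day 4 would be counted.**

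| Event with onset after the last dose | Counted under |
|---|---|
| Death | 30-day mortality |
| Severe event | Severe adverse event (no dosing limit in its sentence) |
| Extrapulmonary, needs treatment | Extrapulmonary complications to day 30 |
| Pulmonary complication, Clavien-Dindo grade II or above | Primary outcome |
| Non-severe, needs no treatment (e.g. dry mouth, dizziness, somnolence, palpitation) | Nothing |

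The gap is the last row. The rule that adverse events are followed until resolved does not close it, because that rule governs how long an event is followed, not when it may start.

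**3. The periods side by side.** The definition uses the dosing period. The second list in the same section uses the perioperative period, without limits. The follow-up section, speaking of treatment of adverse events, uses the study period. These are three different spans, and the article does not say which one governs onset.

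**4. The definition against its list.** The definition requires an event to be unpredictable. The list names dry mouth, flushing, dizziness, palpitation, somnolence and delirium. An event named in advance as a possible effect of the drug is hard to call unpredictable. Someone applying the definition strictly could leave it out, while someone working from the list would record it.

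**The case against.** The strongest reply is that the section works better in practice than its first sentence suggests. The lists name the expected effects, symptoms are sought by non-directive questioning, delirium has a named instrument, and relationship to the intervention is recorded. An investigator who reads the whole section would record dry mouth during dosing. This stands. A reader might infer that expected anticholinergic effects are excluded from the safety data, and the article does not support that. It shows a contradiction in wording.

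A reader might also infer that the safety comparison as a whole stops at the last inhalation. That is not supported either. Mortality and treated complications run to day 30, the severe-event sentence carries no dosing limit, events leading to readmission are recorded, and events already begun are followed to resolution.

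It is also fair to say that the size and direction of any bias are not shown. The article gives no half-life, duration of effect or onset data, so any percentage for late-starting events would be a guess. The point about early stopping depends on reading the dosing period as the individual patient's own, and the sentence does not settle this.

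What the reply does not remove is the rule itself. The defining sentence ties onset to dosing, and the other two descriptions of the period compete with it without correcting it. This is a stated rule, not a detail left to a fuller document.

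**Conclusion.** The point holds in a limited form. As written, non-severe events that begin after the last inhalation and need no treatment are counted nowhere, although patients are seen on four more consecutive days and then weekly. The literal onset window is 72 hours and leaves about 28 of the 30 postoperative days uncovered. The window is described in three inconsistent ways, and the unpredictability condition in both definitions conflicts with the section's own list.

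The conclusion rests on reading the defining sentence literally and on the article's description of the drug as long-acting. The number of events lost, and hence any effect on the between-arm comparison, cannot be computed from the article. The primary outcome is unaffected. The reason to act is that the repair is cheap and the trial is meant to inform on safety.

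**What to change.** - Delete the unpredictability condition from the adverse event and severe adverse event definitions, and record expectedness as a separate field.
- State one onset window for adverse events, from the first inhalation to a fixed day after the last scheduled dose that existing visits cover, for example postoperative day 6. Apply it to every patient whether or not study drug was stopped early, and use the same term for it throughout.
- State that severe adverse events are collected to day 30.
- Report counts by arm for the dosing period and, separately, for the period after it.

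The cost is an amendment to the protocol and CRF wording, a few more entries at visits already scheduled, and some unrelated postoperative events in the table. The split by period keeps those visible. Day 6 is taken from the visit schedule, not from any drug property. Because recruitment began in September 2015, the report should give the date of the change and say which patients were followed under each wording.

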### Sample size calculation

In our recent randomized controlled trial, PPCs occurred in 51.7% of patients in the placebo group [11]. Mazo et al. reported incidences of PPCs from 42.1% to 44.9% in high-risk patients (ARISCAT risk score ≥ 45) [4]. Whereas perioperative inhalation of tiotropium reduced the incidence of PPCs by 16% [6], and inhalation of penehyclidine during the first three postoperative days reduced the incidence of PPCs by 12.4% [11]. In the present study, we assume that the incidence of PPCs will be 42.1% in high-risk patients of the placebo group, and prophylactic penehyclidine inhalation will reduce the incidence of PPCs by 10%. The calculated sample size that will provide 80% power to detect a superiority of this difference at a one-sided significance level of 0.025 is 360 patients in each group. Considering a dropout rate of about 20%, we plan to enroll 432 patients in each group. The sample size calculation was performed with PASS 2008 software.

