**Methods:**

This is a randomized, double-blind, placebo-controlled trial with two parallel arms. A total of 864 patients at high risk of PPCs will be enrolled and randomized to receive prophylactic inhalation of either penehyclidine or placebo (water for injection). Study drug inhalation will be administered from the night (7 pm) before surgery until the second day after surgery, in an interval of every 12 hours. The primary outcome is the incidence of PPCs within 30 days after surgery. Secondary outcomes include the time to onset of PPCs (from end of surgery to first diagnosis of PPCs), the number of PPCs (indicates the number of diagnosed individual PPCs), the incidence of postoperative extrapulmonary complications, the length of stay in hospital after surgery, and the 30-day all-cause mortality.

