Criteria of dropout include the following: (1) consent withdrawn by the participants themselves (at least one dose of study drug has been administered); (2) loss to follow‐up; (3) ordered to exit by the investigators or attending physicians (poor compliance, occurrence of severe complications, or occurrence of severe adverse events); (4) prophylactic use of any prohibited drugs (anticholinergics or any medications other than the study drugs) from study recruitment to postoperative day 2; or (5) blindness unmasked. For dropout cases, detailed reasons will be recorded in the case report forms (CRFs). The primary therapeutic effects recorded the last time will be regarded as the final results. These cases will be included in the intention-to-treat analysis but excluded from the per protocol analysis.

Criteria of rejection include the following: (1) consent withdrawn by the participants themselves (study drug is not administered); (2) no study record; or (3) surgery delayed or canceled, unable to assess the occurrence of PPCs. For rejected cases, detailed reasons will be recorded in the CRFs. These cases will be excluded from analysis of therapeutic effects.

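### The 20% dropout allowance is miscalculated: 432 per group covers a loss of at most 16.7%; keeping 360 after a 20% loss needs 450

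*Protocol article*

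**What the plan says.** All the sample size inputs are in the section Sample size calculation. For the control rate: "we assume that the incidence of PPCs will be 42.1% in high-risk patients of the placebo group". For the effect: "prophylactic penehyclidine inhalation will reduce the incidence of PPCs by 10" percent. The target is 80% power, and the size needed for it is stated so: "at a one-sided significance level of 0.025 is 360 patients in each group". The allowance follows: "Considering a dropout rate of about 20%, we plan to enroll 432 patients in each group". The abstract repeats the total: "A total of 864 patients at high risk of PPCs will be enrolled".

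Two other places decide what a dropout does to the analysis.
- The section Participants lists the dropout criteria, fixes a dropout's outcome at the last recorded result, and says: "These cases will be included in the intention-to-treat analysis but excluded from the per protocol analysis". A separate category, rejected cases (study drug never given, no study record, or surgery delayed or cancelled), leaves the efficacy analysis altogether.
- The section Data analysis, General principles, makes intention-to-treat the basis for all analyses and adds a per-protocol analysis for the primary outcome.

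**The concern.** The base, the dropout rate and the enrolment figure do not agree with one another. If a fraction d of enrolled patients is lost and n must remain, enrolment has to be n / (1 − d). The article's figure matches n × (1 + d), a common slip that always gives too few patients.

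The sample size paragraph also does not say which analysis set the 360 belongs to. An allowance that adds patients for dropout presupposes that dropouts are not analysed. That is true of the per-protocol set, but not of the intention-to-treat set as this article defines it.

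At stake is the accuracy of the power statement against which a null result would be read. As written, a reader takes it that 80% power is secured at 20% dropout, and for an analysis that loses those patients it is not.

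**Working it through.** **Inputs.** From Sample size calculation: p1 = 0.421; one-sided alpha 0.025 (z = 1.960); power 80% (z = 0.842); 360 per group before dropout; dropout about 20%; 432 enrolled per group. The 10% reduction is read as 10 percentage points, so p2 = 0.321. A relative reduction of 10% would need 2125 per group, so the absolute reading is the one intended. From Data analysis: the primary test is a chi-squared test.

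**Step 1: reproduce the 360.** With mean proportion 0.371, the pooled-variance formula is

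n = [1.960 × √(2 × 0.371 × 0.629) + 0.842 × √(0.421 × 0.579 + 0.321 × 0.679)]² / 0.10² = 365.1, so 366.

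The unpooled formula gives 362.4, so 363. Both are within 3% of 360, and power at 360 is 79.4% (pooled) or 79.7% (unpooled). The base figure is reproduced.

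**Step 2: the allowance.**
- As applied: 360 × 1.2 = 432 per group, 864 in total.
- As needed for a 20% loss: 360 / (1 − 0.20) = 450 per group, 900 in total.
- Shortfall: 18 per group, 36 in total.
- Loss that 432 covers: 1 − 360/432 = 16.7%.
- Patients left after a 20% loss: 432 × 0.8 = 345.6, about 346 per group.

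**Step 3: power if the lost patients are not analysed.** Using

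power = Φ{[0.10 × √n − 1.960 × √(2 × 0.371 × 0.629)] / √(0.421 × 0.579 + 0.321 × 0.679)}:

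| Analysed per group | Power, pooled formula | Power, exact chi-squared |
|---|---|---|
| 346 (20% lost from 432) | 77.8% | 78.0% |
| 360 (16.7% lost from 432) | 79.4% | 79.4% |
| 432 (none lost) | 86.2% | 86.4% |

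The slip itself costs 79.4 − 77.8 = 1.6 points.

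**Step 4: power if dropouts are kept, as under intention-to-treat.** All 432 per group count, and what changes is the size of the difference. The dilution is an assumption, because the article does not quantify it. Placebo is held at 42.1%.

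| Share of the 10-point difference lost | Difference | Power at 432 |
|---|---|---|
| 0% | 10.0 points | 86.2% |
| 8% | 9.2 points | 79.9% |
| 10% | 9.0 points | 78.1% |
| 20% | 8.0 points | 67.8% |

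With 20% dropouts who keep a fraction k of the effect, the difference is 10 × (0.8 + 0.2k) points. A loss of 8% therefore corresponds to k = 0.6. The last row, k = 0, means that no penehyclidine dropout benefits at all. It is a bound, not a forecast.

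**The case against.** The strongest reply is that the primary analysis never shrinks to 346. Dropouts are retained with their last recorded result, so 346 is the per-protocol count, or the count if the whole 20% were rejected cases, which the article does not say. This stands. A reader might infer from the slip that the trial does not have its 80% power. The documents do not support that for intention-to-treat: power there is 86.2% undiluted and may end up on either side of 80%.

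Nor do they support treating heavy dilution as the expected case. A patient who withdraws consent counts as a dropout only after at least one dose. Loss to follow-up or unmasking can come after all seven inhalations, since follow-up runs to day 30. Patients who deviate from the intervention are still to be followed up. It would also go too far to assume that every dropout is carried forward as free of PPCs: a PPC recorded before dropout still counts, and severe complications are themselves a reason for dropout.

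A reader might also object to the base of 360, since standard formulas give 363 to 366. That gap is within the variation between formulas, and 79.4% rounds to the stated power, so it is not part of this point.

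Finally, the article says about 20%, and the effect on power is small beside the uncertainty in the inputs: the same paragraph cites placebo rates from 42.1% to 51.7%. The small size is conceded. The approximate rate is not a defence, because 432 equals 360 × 1.2 exactly, which shows how the figure was obtained.

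**Conclusion.** The allowance is wrong as written. It is short by 18 patients per group for the stated rate and covers 16.7% instead of 20%. If 20% are not evaluable, power is about 78%, roughly 2 points below the stated 80%. This conclusion rests on 42.1% against 32.1%, one-sided 0.025 and the chi-squared test, all as planned.

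For the primary intention-to-treat analysis the article shows no shortfall. Power there is 86% with no dilution and drops below 80% only once roughly 8% or more of the 10-point difference is lost, a quantity that the article leaves open. The error is minor in size, but it sits in a figure that the trial relies on and is cheap to put right.

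**What to change.** Keep 864 patients and reword the paragraph in Sample size calculation so that it does the following:
- states that 432 per group preserves 360 evaluable patients up to a loss of about 16.7%, and gives about 78% power at a 20% loss;
- records that a 20% loss would have needed 450 per group (900 in total);
- says which analysis set the 360 refers to;
- gives the intention-to-treat power with dropouts retained, under a stated dilution assumption (for example 86% with none and 78% if a tenth of the difference is lost).

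The cost is one reworded paragraph and a slightly less favourable power statement for the per-protocol analysis. No patients are added, and neither the design nor the analysis changes.
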